## Data collection

### Screening & survey

Prior to the start, a full census of the study population will be carried out with assignment of a unique code number to each individual living in the study area. The whole population will be asked to participate for a free clinical and biological examination for malaria parasites and adequate treatment when required. People will be asked an oral consent in the presence of the village leader and the hamlet health worker, and will be clinically examined by a medical doctor. Body temperature will be checked and a blood sample (finger prick) for microscopic examination (thick+thin film) will be collected. Microscopic examination will be done immediately: all non-P.vivax malaria infections (including all mixed infections) will be treated according to the national guideline, and other pathologies will be treated or referred accordingly. Patients with a *P.vivax* mono-infection, if eligible (see §selection criteria), will be invited to enter in the study cohort for a 2-year monthly follow up (written informed consent required). Non-eligible *P.vivax* patients (including those refusing consent), will still be offered the possibility to be treated free of charge according to the national treatment guidelines (CQ+PQ).

All data will be recorded onto a pre-coded standardised questionnaire (Annex1).

More detailed information on the socio-economic status, preventive measures employed and known malaria risk factors will be collected in one family member randomly chosen by drawing a folded paper containing a number (one number per household dwellers). The chosen number will correspond to the individual code number of the person to be included in the survey. If the chosen individual is absent or refuses to take part, he/she will not be replaced by another household member, the survey procedures will not be done in that household. Every effort will be made to trace an absent survey participant (survey team returning at different times during the whole duration of the survey in that village). After informed consent, the survey participant will undergo a detailed interview on his last months’ activities in relation to malaria exposure, and to preventive measures taken. In addition to the blood slide, one more blood sample will be taken for haemoglobin measurement (Hemocue) and another one on filter paper for later serology and genotyping. Microscopic examination will done on the spot and if a patient is detected with a *P.vivax* mono-infection, he will be invited to enter the cohort following similar procedures as during the screening (selection criteria and informed consent). Non eligible *P.vivax* patients, and other survey participants (with malaria or other diseases) will be treated according to the national guidelines.

All data will be recorded onto a pre-coded standardised questionnaire (Annex2).

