### Cohort recruitment

Vivax infected patients will be recruited during the initial screening/survey and/or during one year of the passive case detection (PCD) continued in each study village during the whole cohort follow-up.

Initially, the recruitment period was foreseen from April 2009 to April 2010. Since only 117 *P.vivax* patients could be recruited by February 2010, it was decided to extend the recruitment until December 2010 in order to reach the target number of 250 patients included.

*Inclusion criteria*

- Age ≥ 3years
- *P.vivax* mono-infection (asexual stages);
- Resident in the study villages;
- Written informed consent (parent/guardian for minors);

*Exclusion criteria*

- General danger signs with severe or complicated malaria according to WHO definitions (Annex B to this protocol);
- Pregnancy (rapid test positive or pregnancy clinically confirmed) or breastfeeding;
- Known G6PD deficiency (or history of “black urine” after previous primaquine treatment), or any history of side effects to the study drug;
- Documented radical cure with Primaquine (10 days at 0.5mg/kg) within one month prior to inclusion;
- Underlying chronic diseases (TB, lupus, diabetes, rheumatoid arthritis, etc);
- Concomitant infectious disease requiring antibiotic treatment;
- Severe malnutrition;
- Patients with neuro-psychiatric disorders or previous history (epilepsy, dementia, ..)

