### Patient discontinuation or protocol violation

Cohort patients meeting any of the following criteria will be classified as **withdrawn**

- **Withdrawal of consent:**

Any patient may withdraw consent at any time, without prejudice for further follow-up or treatment in the study site.

- **Failure to complete the treatment due to either:**
- Failure to attend the scheduled visits during the 10-day treatment;
- Serious adverse events necessitating termination of the treatment before the full course (10 days) of the treatment is completed;

A patient who vomits twice the study medications will be withdrawn from the study and given the rescue treatment.

A patient can be discontinued from the study if the investigator decides that a patient should be withdrawn for safety reasons due to serious adverse events (signs of hemolytic anemia (yellow conjonctives/dark urine) or Grade 3 to 4 of the WHO classification for adverse events). In this case, information concerning the adverse event and symptomatic treatment given must be recorded on the patient follow-up form (Annex 7).

- **Voluntary protocol violation (28-day follow-up)**

Self- or third party administration of antimalarial (or antibiotics with antimalarial activity such as tetracycline, amoxicilline).

- **Involuntary protocol violation (during the 28-day follow-up)**
- Occurrence of concomitant disease that would interfere with a clear classification of the treatment outcome;
- Detection of another malaria species during the follow-up;
- Erroneous inclusion of a patient who do not meet the inclusion criteria;
- Misclassification of a patient due to a laboratory error (parasitaemia) leading to the administration of the rescue treatment;

**Patients who are withdrawn will be followed up until day 28 and continue the 2-year monthly follow-up.** However, no treatment outcome will be assigned to these patients during the 28-day follow-up. The reason for discontinuation or protocol violation will always be recorded on the follow-up forms (Annex 7 or Annex 8, accordingly).

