***Treatment of patients in the cohort***

The new treatment guideline for the radical cure of *P.vivax* (2007) consists of 25mg/kg Chloroquine (CQ) over 3 days, together with Primaquine (PQ), 0.5mg/kg daily for 10 days, under the direct supervision of the study team (Table 1). Patients will be observed during one hour: in case of vomiting within the first 30 minutes, a full dose will be re-administered, only half dose if vomiting occurs between 30 minutes and 1 hour. The total number of tablets of each drug administered (+/- re-administrated dose if vomiting) will be recorded on the patient’s follow-up form (Annex7)

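### The screening section offers chloroquine plus primaquine to every non-eligible P. vivax patient, without setting apart those excluded for evident primaquine-safety reasons

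*Protocol*

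**What the plan says.** Three parts of the protocol bear on this.

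- **Section 3.3.1, Screening & survey (whole-population screening).** P. vivax mono-infections that meet the selection criteria are invited into the cohort. For the rest, the text says that non-eligible patients (a bracket includes those who refuse consent among them) "will still be offered the possibility to be treated free of charge according to the national treatment guidelines (CQ+PQ". The section refers to the selection criteria for the meaning of eligible.
- **Section 3.2.1, Cohort recruitment (exclusion criteria).** The list includes "Pregnancy (rapid test positive or pregnancy clinically confirmed) or breastfeeding" and "Known G6PD deficiency (or history of “black urine” after previous primaquine treatment), or any history of side effects to the study drug". It also includes severe or complicated malaria with danger signs, and a documented primaquine radical cure within the previous month.
- **Section 3.3.1, random-sample survey.** Non-eligible P. vivax patients found in the survey are to be treated under the national guidelines. No regimen is named there.

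**The concern.** The offer covers the whole non-eligible group. Those who refuse consent are only one part of it, as the word introducing them in the bracket shows. Other parts are patients kept out because of G6PD deficiency or a previous reaction. A field team that follows the sentence as written would offer primaquine to someone excluded for black urine after primaquine.

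What is at stake is patient safety and the clarity of a field instruction. Screening is directed at the whole study population, so such patients may be met. The protocol describes supervised dosing and checks for haemolysis for cohort patients and describes nothing comparable for patients treated outside the cohort. That is silence about their follow-up; it does not show that they would have none.

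**Working it through.** The check is textual, and the plan has no figure to reproduce.

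**Step 1: who is non-eligible.** Anyone failing section 3.2.1. This is a mixed group: refusers, children under 3 years, patients with severe malaria, patients recently given radical cure, pregnant or breastfeeding women, and patients with G6PD deficiency or an earlier reaction.

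**Step 2: what they are offered.** Section 3.3.1 names one regimen for all of them. Section 3.3.3 describes the national radical-cure regimen as chloroquine with "Primaquine (PQ), 0.5mg/kg daily for 10 days, under the direct supervision of the study team". The primaquine abbreviation in section 3.3.1 therefore reads most naturally as that same course.

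**Step 3: how firmly each exclusion is tied to primaquine.**

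| Exclusion | Link to primaquine in the text |
| --- | --- |
| Black urine after earlier treatment | Explicit: primaquine is named |
| Known G6PD deficiency | By placement: same bullet as the black-urine item |
| Side effects to the study drug | Same bullet; drug not named, and the cohort receives two |
| Pregnancy, breastfeeding | No reason stated; a safety purpose is inferred |

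**Step 4: whether the protocol treats haemolysis as a hazard.** It does. Section 3.2.3 gives "signs of hemolytic anemia (yellow conjonctives/dark urine" as a ground on which the investigator may withdraw a patient for safety. Section 3.3.3 has urine and conjunctivae checked in cohort patients, and Table 2 schedules haemoglobin on days 0, 14 and 28. Annex C lists drugs to avoid during primaquine treatment.

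**Step 5: whether any other text limits the offer.**

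- The survey sentence in section 3.3.1 refers to the national guidelines and names no regimen, so the difficulty does not arise there.
- Section 3.3.2 (passive case detection and monthly active detection) does not say how a non-eligible P. vivax mono-infection is treated. It neither repeats nor restricts the offer.
- Section 4 (Ethical issues) promises adequate treatment to people who refuse to take part. That concerns refusers and says nothing about patients excluded for safety.

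No section restricts the offer by reason for exclusion.

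**Step 6: how many patients.** Section 3.2.6 gives a P. vivax prevalence of 9% and a population of 2,100, so 0.09 × 2,100 = 189 infections might be found if everyone were screened. The next step needs the share of those 189 who meet a safety-related exclusion. The protocol gives no G6PD prevalence, no frequency of earlier reactions, and no proportion pregnant or breastfeeding. The count cannot be taken further.

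**The case against.** A reader might infer that the sections contradict each other on safety. They do not, strictly. Section 3.2.1 decides who enters the cohort and nowhere forbids primaquine outside it. One section concerns enrolment and the other routine care, so what remains is a sentence lacking a qualification that the exclusions call for. This objection stands.

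A second objection is that the operative rule is the national guideline, with the bracket only a label for the usual vivax regimen. If the guideline has its own exceptions, following it would protect these patients. The literal reading also proves a great deal: it would send patients with severe malaria to the same regimen, although section 3.2.4 directs parenteral treatment for any sign of severe malaria in cohort patients. That suggests shorthand. The objection lowers the likelihood of harm, but it does not cure the wording. The guideline is not in the documents, and the protocol itself tells the team what it means here, without exception.

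Third, section 3.3.1 has a medical doctor examine everyone screened and promises adequate treatment. A picture of untrained staff handing out primaquine is not supported. The doctor is a real safeguard, though one that works by departing from the written instruction.

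Two wider readings are also tempting. One carries the fault over to the survey sentence and to passive and monthly active detection; the first names no regimen and the second gives no such instruction, so neither shares it. The other puts a number on the patients at risk. Assuming 5% to 10% of 189 gives 9.45 to 18.9, or about 9 to 19 people, but no statement in the protocol supports that share. Meeting an exclusion is also not the same as being given primaquine.

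**Conclusion.** The concern holds as a fault in one instruction. The screening text of section 3.3.1 offers chloroquine plus primaquine to all non-eligible P. vivax patients, and no text in the protocol limits that offer for patients excluded on evident primaquine-safety grounds. The case is strongest for black urine after primaquine and known G6PD deficiency. It rests on inference for pregnancy and breastfeeding.

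The conclusion assumes that the bracket is read as written and that primaquine there means the regimen described in section 3.3.3. If the national guideline carries exceptions and the examining doctor applies them, the practical risk may be small; the documents do not allow this to be judged. The size in patients is unknown. The primary and secondary endpoints and the sample size are unaffected, since the patients concerned are outside the cohort. The point merits correction because the possible harm is serious and the remedy is simple.

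**What to change.** Reconcile the screening sentence in section 3.3.1 with the exclusion criteria in section 3.2.1:

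1. Separate patients who are non-eligible only because they refuse consent from those excluded for a safety reason.
2. Remove the blanket bracketed regimen for the second group. The survey sentence in the same section already avoids the problem by naming no regimen.
3. Have the responsible clinicians decide, with the national guideline in hand, what the text should say for each excluded group. This review does not judge which treatment is right.

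The cost is a one-sentence amendment and a short instruction to the screening team. No change to sampling, data collection or analysis follows.

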### Passive case detection of *P.vivax* patients

Before the start of recruitement, all HHWs from the 4 study villages and the Tra Leng CHC staff will be trained to detect malaria patients with a rapid test, subsequently confirmed by microscopy reading, in order to complete the *P.vivax* patients’ recruitment. Symptomatic patients from the 4 study villages will be able to consult either their respective HHW or the CHC in Tra Leng for malaria diagnosis and treatment. At village level, malaria detection will be done with rapid diagnosis tests (RDT), secondarily confirmed by microscopic examination at the CHC before treatment administration. Patients will be first interviewed on malaria signs and treatments taken prior consulting, their body temperature checked, and blood samples for RDT and blood slide (thick+thin film) will be taken. Antipyretic treatment can be delivered before the slide results. If the patient presents with acute malaria symptoms and the RDT is positive for P.falciparum, he will be treated with Arterakin for 3 days following the national treatment guideline. If a patient is found positive with a P.vivax mono-infection, if eligible he will be invited to enter the cohort, after written informed, and will be treated and followed-up accordingly. Patients with mixed Pv infections or other malaria species will be treated according to the national guidelines (Arterakin 3 days if P.falciparum is present, CQ 3days for non Pf species) and other patients will be referred to the CHC if necessary. HHWs will only have the possibility to treat either malaria infections and/or simple viral infections treatment (antipyretic/painkiller). All data will be recorded onto a pre-coded standardised questionnaire (Annex9).

In addition to the PCD, monthly active detection of malaria cases was initiated in June 2009 in order to reinforce the recruitment process by PCD (low skills of HHWs). Once a month, each household is visited by the study team, and all febrile individuals get sampled (thick & thin film) in order to screen for malaria parasite. *Pvivax* mono-infecgtions are recruited into the cohort if eligible, Pf or mixed infections are treated according to the national guidelines.

### *P.vivax* patients’ treatment & cohort follow-up

Patients identified during either the initial screening/survey or during PCD and fulfilling all the inclusion criteria (all present) and exclusion (all absent) criteria will be included in the cohort. They will be treated with a 10-day radical cure regimen of Primaquine, and will be monitored during the first 28 days following standard WHO protocol for *in vivo* antimalaria drugs efficacy studies, then monthly checked for malaria symptoms and parasites for 23 months.

***Treatment of patients in the cohort***

The new treatment guideline for the radical cure of *P.vivax* (2007) consists of 25mg/kg Chloroquine (CQ) over 3 days, together with Primaquine (PQ), 0.5mg/kg daily for 10 days, under the direct supervision of the study team (Table 1). Patients will be observed during one hour: in case of vomiting within the first 30 minutes, a full dose will be re-administered, only half dose if vomiting occurs between 30 minutes and 1 hour. The total number of tablets of each drug administered (+/- re-administrated dose if vomiting) will be recorded on the patient’s follow-up form (Annex7)

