**SUMMARY**

*Plasmodium vivax* is the most widely spread of the four malaria species and the main cause of malaria outside Sub-Sahara Africa. In Central Vietnam, nearly 50% of malaria infections are due to *P.vivax*, causing a heavy morbidity burden for the local population due to the activation (relapse) of dormant liver forms (hypnozoites) weeks or months after the primary infection. The national guideline for the radical cure of *P.vivax* infection was changed in 2007, with an increase of the daily dose of primaquine from 0.25mg/kg to 0.50mg/kg for 10 days (the 3-day concomitant chloroquine regimen (total 25mg/kg) remaining unchanged). The efficacy of this new regimen in preventing short as well as long term relapses has not been evaluated yet. Moreover, the epidemiology and the transmission dynamics of *P.vivax* remains poorly documented due to the lack of reliable tools to distinguish between new infections, recrudescence and relapses. Consequently, as control strategies cannot be adequately adapted to the local epidemiology, *P.vivax* morbidity continues to contribute to the vulnerability of the local populations, mainly ethnic minorities, with poor health and socio economic status. The main objective of this study is to establish a new tool that will assist the National Malaria Control Program to improve control strategies for *P.vivax* in Vietnam. This tool will be based on molecular (microsatellites) and serological (CSP ELISA) techniques and on mathematical modelling, to distinguish between a new infection, and a relapse/recrudescence of *P.vivax*. A cohort of 250 *P.vivax* infected patients will be treated and followed up for 2 years in order to estimate the efficacy of the current treatment guideline in preventing recrudescence and relapses, and determine the incidence of new infections. The development of such a tool is extremely important for the control of *P.vivax* in Vietnam since it will help to understand the epidemiology of *P.vivax* and to test targeted interventions, including new drugs. Eventually, the National Malaria Control Program will be able to adapt its control strategies and monitor the efficacy of the treatment guidelines. This study will be conducted concomitantly to a similar one in the Peruvian Amazon (“sister project”), in order to compare the results and to validate the new tool. In addition, this project will contribute to strengthen the institutional collaboration between NIMPE, Hanoi and ITM, Antwerp with the training of 2 Vietnamese junior scientists (1 Msc and 1 PhD), and to develop a new South-South collaboration between the NIMPE, Hanoi and ITM-AvH, Lima, through simultaneous training of 2 Peruvian students. Exchange of information, experience and expertise on *P.vivax* between the 2 southern institutions is likely to boost new perspectives in R&D in 2 endemic regions facing similar challenges for malaria control.

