### Sample size calculation

Two different sample sizes were calculated: one for the estimation of *P.vivax* failure rate for chloroquine (28-day follow-up) and for Primaquine (2-year follow-up) in a cohort of *P.vivax* patients initially treated with the current radical cure regimen, and the second for the population survey on *P.vivax* prevalence (in a random sample of the study population).

- ***P.vivax population survey***

A total2,100 individuals at risk of malaria were estimated in the 4 study communes (census February 2009). According to the provincial malaria station (PMS) data on surveys carried out in April-May, the overall parasite rate was around 16% (ranging from 5 to 39% across hamlets) and the prevalence of *P.vivax* at 9%. In order to detect a minimal prevalence of 9% with 3% precision and at 5% significance level, a total of 300 individuals is needed for the survey (“CSample” command/EpiInfo6). After “finite population correction” and adding 10% security margin, a final sample size of 300 individuals would be sufficient. Since there are a total of about 370 households and in order to simplify sampling procedures, one individual in each house visited for the screening will be randomly selected to participate in the survey. This will be done by randomly choosing from the census file. The selected individual will be asked oral informed consent before starting in-depth interview.

- ***P.vivax cohort***

Between 2003 and 2007, *P. vivax* late parasitological failure to CQ was monitored in several Central Vietnam provinces and ranged from 0% to 5.7% (13). Therefore, to detect a failure rate as low as 5% with a 3% precision at 5% significance level, a minimum of 185 individuals are needed (“CSample” command/EpiInfo6). Assuming a maximum drop out rate of 10% during the first 28 days, a total of 204 cases will be necessary. For the estimation of a similar PQ failure rate after 2 years of follow-up, a total of 230 patients should be included with a maximum of 20% drop out during the 2-year follow-up.

By including 250 vivax patients in the cohort, and assuming a maximum drop out rate of 20% during the 2-year follow-up, we can expect to get a final database of 200 patients with a complete follow-up (i.e. 31 successive sampling results) for the modelling of *P.vivax* new infections/relapses.

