**Table 1: Doses of CQ & PQ by body weight**

| **Weight (kg)** | **Primaquine base, 7.5 mg**  **Number of tablets/day**  **(Total = 10 days)** |
| --- | --- |
| **5-6** | 1/4 |
| **7-10** | 1/2 |
| **11-14** | 3/4 |
| **15-18** | 1 |
| **19-21** | 1+1/4 |
| **22-25** | 1+1/2 |
| **26-29** | 1+3/4 |
| **30-33** | 2 |
| **34-36** | 2+1/4 |
| **37-40** | 2+1/2 |
| **41-44** | 2+3/4 |
| **45-48** | 3 |
| **49-51** | 3+1/4 |
| **52-55** | 3+1/2 |
| **56-59** | 3+3/4 |
| **60+** | 4 |

| **Weight (kg)** | **Chloroquine base, 150mg**  **Number of tablets** | | |
| --- | --- | --- | --- |
| **Day0** | **Day 1** | **Day 2** |
| **5-6** | 1/2 | 1/4 | 1/4 |
| **7-10** | 1/2 | 1/2 | 1/2 |
| **11-14** | 1 | 1 | ½ |
| **15-18** | 1 | 1 | 1 |
| **19-24** | 1.5 | 1.5 | 1 |
| **25-35** | 2.5 | 2.5 | 1 |
| **36-50** | 3 | 3 | 2 |
| **50+** | 4 | 4 | 2 |

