**Day 0: Enrollement/ administration of the study medication**

Demographic Data and Medical History

Demographic data and a general history of past and present illnesses will be recorded onto to the pre-coded standardised form for the 28-day follow-up.

Informed consent

After an in-depth interview, with one physician of the study or with another qualified person, the patient (or the parent/legal guardian) will be asked to document his/her consent by signing an informed consent form; if the patient is minor of age/not emancipated, the consent must be given by a parent or legal guardian according to national law. However, in this case, the investigator is responsible to check that the patient is also freely willing to take part in the study. The signed informed consent (or thumb-printed whenever the patient or the parents/guardians are illiterate) must be obtained before any tests or evaluations related to the study are carried out. However, a thick blood film or a rapid diagnostic test before the informed consent can be done as this can be considered a normal procedure for the management of patients suspected having clinical malaria.

Physical and Clinical Examination

A general physical examination will be performed.

A clinical examination will be performed: symptoms and axillary temperature (mercury thermometer).

Vital Signs and Weight

Vital signs (respiratory rate and pulse) and weight will also be measured (see details in patient’s form for 28-day follow-up).

Blood slides:

Thick and thin films will be prepared following the SOP (standard operating procedures) for laboratory. Blood slides will be examined for the confirmation of *P. vivax* mono-infection and parasite density.

Blood slides will be independently read by 2 qualified microscopists, data entered in separate files. Further details are described and explained in the SOP (SOP: Quality control (QC) guidelines for the laboratories participating in the study).

Parasite density will be calculated by counting the number of asexual parasites per 200 leukocytes in the thick blood film, based on an assumed WBC of 8,000 /µl by light microscopy at 1000xmagnification. The parasite density per microlitre will be calculated using the following formula:

Parasite density / µl = Number of parasites counted x 8,000

Number of leukocytes counted

PCR/ELISA

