A blood sample (2 spots of at least 1.5cm diameter) will be collected on filter paper (Whatmann grade 3) at day 0 before treatment and every time a blood slide is done. Samples from patients classified as late treatment failure will be subsequently used for parasite genotyping. ELISA test for detecting CSP protein will be done on all blood samples at of the 28-day and monthly follow-up. Antibodies against the CSP are specifically produced during a new *P.vivax* infection (but not during relapses).

Haemoglobin (Hb)

Haemoglobin will be measured directly by using the HemoCue method following the SOP for laboratory. Briefly a drop of capillary blood is taken with a microcuvette which is then put in the reader. After 10” the Hb level appears on the screen. The result is directly recorded on the patient’s form.

Blood sample for CQ blood level measurement

100µl of capillary blood is taken with a microcapillary and poured onto a filter paper (Whatman grade 3).

Administration of the Study Drugs by a study doctor or nurse

CQ and PQ according to the patient’s body weight (Table 1).

Adverse Events Report

All adverse events will be recorded.

Concomitant Medications

Any medications taken by the study subject will be recorded.

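### Table 1 places a 50 kg patient in two chloroquine bands, 1200 mg or 1500 mg, with no rule for choosing between them

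*Protocol*

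**What the plan says.** The Protocol's Summary describes "the 3-day concomitant chloroquine regimen (total 25mg/kg) remaining unchanged", so 25 mg/kg is a total over three days, not a daily dose. Section 3.3.3, under the treatment of patients in the cohort, repeats that the guideline regimen "consists of 25mg/kg Chloroquine (CQ) over 3 days" and refers to Table 1. Under Day 0, the instruction for giving the study drugs is "CQ and PQ according to the patient’s body weight (Table 1"), so staff dose from the table and do not calculate from mg/kg.

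The chloroquine half of Table 1 is headed "Chloroquine base, 150mg" and lists tablets for Days 0, 1 and 2 by weight band. The last two rows are 36-50 kg (3, 3 and 2 tablets) and 50+ kg (4, 4 and 2 tablets). The protocol gives no rule for a weight that meets both labels, and no tolerance around 25 mg/kg.

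Two data items bear on the consequences. At Day 0, "Vital signs (respiratory rate and pulse) and weight will also be measured". During treatment, "The total number of tablets of each drug administered" is recorded, including any dose repeated after vomiting.

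**The concern.** A dosing table has to give one dose for each weight. At 50 kg this one gives two, and which the patient receives depends on the row the staff member reads. Fifty kilograms is a plausible adult weight.

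Chloroquine dose also matters to what the study estimates. Treatment failure at day 28 is one of the two primary endpoints (section 3.2.5), and section 3.2.6 sizes the cohort partly to estimate the "failure rate for chloroquine (28-day follow-up"). Two patients of the same weight could contribute to that estimate on doses that differ by a quarter, with the protocol followed in both cases.

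**Working it through.** **Inputs.** Tablet strength (150 mg base), bands and tablet counts come from Table 1. The total of 25 mg/kg comes from the Summary and section 3.3.3.

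**Formula.** Dose in mg/kg = (tablets on Day 0 + Day 1 + Day 2) × 150 / weight in kg.

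**At 50 kg.**
- Band 36-50: (3 + 3 + 2) × 150 = 1200 mg; 1200 / 50 = 24.0 mg/kg.
- Band 50+: (4 + 4 + 2) × 150 = 1500 mg; 1500 / 50 = 30.0 mg/kg.
- Difference: 1500 − 1200 = 300 mg, or 6 mg/kg; 300 / 1200 = 25% of the lower dose.
- Stated target: 25 × 50 = 1250 mg. The lower row is 50 mg under it and the upper row 250 mg over.

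**Is the overlap a convention of the table?** No. The other chloroquine bands follow one another without overlap, and so do all 16 primaquine bands. The primaquine half ends with 56-59 and then 60+. There the plus sign must mean that weight and above, or a 60 kg patient would have no dose. Read the same way, the chloroquine 50+ row includes 50 kg.

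**How the table relates to 25 mg/kg.** The range 11 to 60 kg is assumed here for illustration, because the protocol gives no weight distribution.

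| Weight (kg) | Tablets | Total (mg) | mg/kg, lightest to heaviest |
|---|---|---|---|
| 11-14 | 2.5 | 375 | 34.1 to 26.8 |
| 15-18 | 3 | 450 | 30.0 to 25.0 |
| 19-24 | 4 | 600 | 31.6 to 25.0 |
| 25-35 | 6 | 900 | 36.0 to 25.7 |
| 36-50 | 8 | 1200 | 33.3 to 24.0 |
| 51-60 | 10 | 1500 | 29.4 to 25.0 |

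Taking 50 kg in the lower band, 25 mg/kg works roughly as a floor in this range. Only 49 kg (1200 / 49 = 24.5) and 50 kg (24.0) fall below it, and 18, 24, 48 and 60 kg meet it exactly. That leaves 50 − 2 − 4 = 44 of the 50 whole weights above it. The highest value is 36.0 mg/kg, at 25 kg. The unweighted mean is 28.5 mg/kg over 11 to 60 kg and 26.9 mg/kg over 40 to 60 kg. Above 60 kg the dose is always below 25 mg/kg (1500 / 61 = 24.6).

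**After relabelling the top band 51+.** A 50 kg patient receives 1200 mg (24.0 mg/kg) and nothing else in the table changes.

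**The case against.** On the overlap, the best reply is that the 36-50 row names 50 explicitly, so 50+ can be read as above 50. Many staff might read it that way, but the primaquine half of the same table uses the sign in the other sense, and no text settles the matter. It is also fair to say that the problem is confined to one recorded weight, and that both candidate doses lie within the 24 to 36 mg/kg that the table gives to other patients. Neither dose is shown to be unsafe or ineffective. These points limit the importance of the overlap without removing it.

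A reader might go further and infer that the 25 mg/kg label is wrong, because 44 of 50 whole weights receive more. The documents do not support that:
- Sections 2.2 and 3.2.5 make the national treatment guideline the thing evaluated, and section 3.3.3 gives the mg/kg figure together with the printed table. A target delivered in whole and part tablets by weight band is nominal by construction, and setting it near the bottom of each band can be a deliberate guard against underdosing.
- The count depends on the chosen range and counts weights, not patients. Extended to 70 kg it becomes 44 of 60.

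Nor can the 25-35 kg row be called an error because it gives the highest dose, since the national guideline table is not shown. Finally, deriving each patient's received mg/kg is a reporting matter. Weight and tablets are already recorded, so its absence from the protocol is no defect.

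**Conclusion.** The overlap at 50 kg is a real but minor error in the dosing table: one weight, two doses 300 mg apart, and no rule to choose. It rests only on the printed labels and on reading the plus sign as the table itself uses it, so it holds whatever the cohort's weights turn out to be. How many patients it would affect cannot be said.

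That the bands usually deliver more than 25 mg/kg up to 60 kg supports no more than an optional change of wording. A reader might infer that the day-28 failure estimate is biased. The protocol gives no dose-response figure, so neither a size nor a direction of effect can be claimed. The sample size is unaffected.

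**What to change.** Make the last two chloroquine bands in Table 1 disjoint, for example 36-50 and 51+, after checking which side of the boundary 50 kg takes in the national guideline table. This costs one label and a notice to the staff who give the drugs, with no new visits, samples or data items.

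Optionally, add a few words in section 3.3.3 to say that 25 mg/kg is the nominal target, delivered through the weight bands of Table 1.
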